## Objectives {7}

The main objective of the trial is to test whether our newly developed digital treatment (Huddinge Online Prolonged Exposure; HOPE) is more effective than the active comparator in reducing PTSD symptoms. The trial will also include a health-economic evaluation from both the treatment provider perspective (i.e., direct costs such as costs for healthcare personnel) and a broader societal perspective (i.e., indirect costs such as sick leave). We will also investigate processes of change during treatment and predictors of treatment outcome.

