### Outcomes {12}

The primary outcome measure is the CAPS-5, the gold-standard clinical interview that evaluates the severity of PTSD symptoms and determines the presence of PTSD in the past month [12]. This evaluation will be conducted at multiple time points: upon enrollment, 1 month after completing the treatment (primary endpoint), and during the 6- and 12-month follow-up assessments. The CAPS-5 total severity score has been shown to exhibit strong internal consistency (Cronbach’s *α* = 0.88) and interrater reliability (intraclass correlation coefficient = 0.91), along with favorable test–retest reliability (intraclass correlation coefficient = 0.78) [12]. Treatment response will be considered achieved if there is a minimum of 10 points improvement on the CAPS-5 between baseline and the participant’s last available measurement within the baseline to 12-month follow-up period (adapted from [13]). Remission will be defined as the absence of a PTSD diagnosis or a CAPS-5 total symptom severity score below 12 [13]. To be classified as having achieved recovery, participants must maintain their remission status at both the 6-month and 12-month follow-ups.

Secondary self-rated outcome measures include the Posttraumatic Stress Disorder Checklist for DSM-5 (PCL-5) [14] and the International Trauma Questionnaire (ITQ) [15] to capture self-rated symptoms of PTSD and complex PTSD. The Patient Health Questionnaire (PHQ-9; [16]) and the EuroQol 5-dimensions (EQ-5D; [17]) will be used to assess the level of depressive symptoms and quality of life. Treatment response on the PCL-5 will be defined as a drop of 10 points or more. For remission, a score below 30 will be used, which has been identified as indicative of probable PTSD in the Swedish version of the PCL-5 [18].

To calculate quality-adjusted life-years for cost-utility analysis, participants will complete the Assessing Quality of Life 6 Dimensions (AQoL-6D; [19]). Data concerning the utilization of medical resources, medication, social care, absenteeism, and presenteeism in relation to employment will be collected using The Treatment Inventory of Costs in Patients with psychiatric disorders (TIC-P; [20]). Moreover, information on adverse events will be gathered using the Negative Effects Questionnaire (NEQ) immediately after treatment completion and the upcoming assessment points [21]. Participants will also receive an open-ended question asking for the occurrence of adverse events weekly during treatment.

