## Statistical methods

### Statistical methods for primary and secondary outcomes {20a}

The data analyses will be carried out by an independent statistician who is not part of the research group. This statistician will also remain blind to the group allocation throughout the duration of the trial. The intention-to-treat approach to the analysis population will be applied in all cases unless specified otherwise. The significance level for all statistical tests will be *α* = 0.05.

For our primary research questions, we will fit a linear mixed-effects model for repeated measures to evaluate change in CAPS-5 total scores within and between groups over time. Fixed effects will include treatment, time, and the treatment × time interaction; a participant-specific random intercept will be specified. An unstructured within-participant covariance will be used, allowing distinct correlations between all pairs of time points. The model will be estimated by restricted maximum likelihood and will use all available observations, yielding unbiased estimates under missing at random or missing completely at random assumptions. The primary hypothesis will be tested two-sided at *α* = 0.05. No adjustments will be made for multiplicity.

As a complementary check at the primary endpoint, we will fit a linear regression of change in CAPS-5 from baseline to 1-month on randomization arm, adjusting for baseline CAPS-5.

We will report within- and between-group effect size (Cohen’s *d*) with 95% CIs. Effects will be deemed statistically significant at *p* < 0.05. Magnitudes will also be described using conventional benchmarks: small (0.20), medium (0.50), large (≥ 0.80).

Crossover participants continue all scheduled outcome assessments. Post-crossover data are obtained as part of a naturalistic follow-up.

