#### Secondary outcomes and analyses

Unless stated otherwise, analyses mirror the primary modelling strategy: continuous outcomes will be analyzed with linear mixed-effects models using all available observations and yielding unbiased estimates under MAR/MCAR. Binary (and ordinal) outcomes will be analyzed with mixed-effects logistic (or cumulative-logit) models; cross-sectional categorical comparisons will use *χ*^2^ or Fisher’s exact tests as appropriate. Effect sizes will be reported as model-based standardized mean differences (Cohen’s *d*) for continuous outcomes and odds ratios for binary outcomes, each with 95% CIs. All secondary analyses are exploratory and *p*-values are nominal (no additional multiplicity adjustment).

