### Methods for additional analyses (e.g., subgroup analyses) {20b}

We will explore differences in treatment effects by gender in a subgroup analysis by including an interaction term between treatment arm and gender. Exploratory mediation will evaluate whether change in emotional responding, adherence, post-traumatic cognitions, avoidance, and alliance mediates treatment effects on CAPS-5. Moderation by baseline demographics and clinical history (e.g., PTSD/CPTSD severity, trauma type and timing, childhood adversity, comorbidity, perceived threat, education, employment, credibility/alliance) will be tested via treatment × covariate interactions; for prognostic models of CAPS-5 response, logistic regression will be used with model calibration assessed by Hosmer–Lemeshow and calibration plots.

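### The only prognostic model named in {20b} is logistic regression on a 10-point cut of CAPS-5 improvement, which discards at least about a third of the information in a score held on its full scale

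*Protocol article*

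**What the plan says.** The protocol article lists prediction among its aims in Objectives {7}: "We will also investigate processes of change during treatment and predictors of treatment outcome". Section {20b} then names a method: "for prognostic models of CAPS-5 response, logistic regression will be used", with calibration to be checked by Hosmer–Lemeshow and calibration plots. Response is defined in Outcomes {12}: "Treatment response will be considered achieved if there is a minimum of 10 points improvement on the CAPS-5", counted from baseline to "the participant’s last available measurement within the baseline to 12-month follow-up period".

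Three other statements bear on how far this reaches:

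- The primary model in {20a} uses the full scale, to "evaluate change in CAPS-5 total scores within and between groups over time".
- Moderation by baseline variables, in the same sentence of {20b} as the prognostic models, "will be tested via treatment × covariate interactions". The outcome scale is not stated there.
- The section on secondary outcomes sets a default, "Unless stated otherwise, analyses mirror the primary modelling strategy", and gives the status of these analyses: "All secondary analyses are exploratory and *p*-values are nominal".

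**The concern.** A 10-point cut treats a 9-point improvement as no response and counts a 10-point improvement the same as a 30-point one. The prognostic question does not need that loss, because the total score is collected and already modelled as continuous.

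The sample was sized for one between-arm contrast, so precision for predictors is whatever that sample happens to give. Reducing it further makes a real predictor of modest strength more likely to be missed, and makes a null result harder to interpret.

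The default to linear mixed models does not remove the problem. It applies only where nothing else is stated, and for prognostic models of response {20b} states something else. The interaction tests ask who gains more from HOPE than from the control, which is a different question from who does well.

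**Working it through.** **Inputs from the article.** d = 0.35, 80% power, two-sided α = 0.05, 1:1 allocation, 10% attrition, 129 per arm retained (Sample size {14}); two-sided α = 0.05 ({20a}); cut at 10 points ({12}).

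**Inputs assumed.** The article gives no predictor strength, response rate, CAPS-5 standard deviation or correlation between baseline and follow-up. The ranges used are stated below.

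**The plan's own figure.** n per arm = 2 × (1.960 + 0.842)² / 0.35² = 128.1, so 129, as stated. Inflation gives 129 / 0.9 = 143.3. The stated 143 per arm retains 0.9 × 143 = 128.7, which agrees to rounding. N = 2 × 129 = 258 is used below. The article states no power for the prognostic models.

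**Information kept by the cut.** For a normally distributed score and response rate p, with z_p the normal quantile at p and φ the normal density, a correlation r with the score shrinks to r × f, where f = φ(z_p) / √(p(1 − p)). Relative efficiency is f².

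- p = 50%: f = 0.3989 / 0.5 = 0.798, f² = 0.64
- p = 30% or 70%: f² = 0.58
- p = 20%: f² = 0.49

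The best case, 50% response, loses 1 − 0.64 = 36%.

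**Power.** By Fisher's z, power ≈ Φ(atanh(r) × √(N − 3) − 1.96). For r = 0.15 on the full scale: 0.1511 × √255 = 2.41, and Φ(0.45) = 67.5%. After a cut at 50% response, r × f = 0.15 × 0.798 = 0.120; 0.1203 × 15.97 = 1.92, and Φ(−0.04) = 48.4%.

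| r | Full scale | Cut, 50% response | Cut, 30 or 70% | Cut, 20% | Loss (points) |
|---|---|---|---|---|---|
| 0.10 | 36.0% | 24.8% | 22.9% | 20.1% | 11 to 16 |
| 0.15 | 67.5% | 48.4% | 44.6% | 39.1% | 19 to 28 |
| 0.175 | 80.6% | 61.2% | 56.9% | 50.2% | 19 to 30 |
| 0.20 | 89.9% | 72.9% | 68.5% | 61.4% | 17 to 28 |
| 0.25 | 98.3% | 89.8% | 86.6% | 80.6% | 8 to 18 |
| 0.30 | 99.9% | 97.4% | 95.9% | 92.6% | 2 to 7 |

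**Check with fitted logistic models.** In 3,000 simulated trials per setting, with one predictor and no covariates, the losses for r = 0.15 were 24, 19 and 20 points at response rates of 30, 50 and 60%. For r = 0.20 they were 21, 18 and 20 points.

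**Check with covariates.** Both models were then adjusted for baseline CAPS-5 and arm. The assumptions were SD 10, arm effect 0.35 SD, baseline to follow-up correlation 0.3, 0.5 or 0.7, mean improvement 5, 10 or 14 points, and a predictor worth 0.12, 0.15 or 0.20 SD of the follow-up score per SD. Response rates came out at about 26 to 69%. The full-scale model gained roughly 6 to 31 points over the 27 settings. At correlation 0.5 and about 50% response, power for a 0.15 SD predictor was about 0.81 against 0.55. The gain was smallest where full-scale power was already above 99%.

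**The case against.** Much of the case on the other side stands.

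- **Scope.** A reader might infer that the whole predictors objective is tied to the binary outcome. The article does not show that. It says only that models of response are logistic, which is the ordinary match for a binary outcome. The moderation tests fall by default in the continuous model, which would ordinarily carry each covariate's own term. What remains is that no continuous prognostic model is named, while a logistic one is.
- **Candidate list.** The long list of baseline variables in {20b} might be read as the candidates for the prognostic model. It belongs to the moderation clause, so no argument about the number of predictors can rest on it.
- **Purpose.** Calibration checks suit a model meant to predict the probability of response, and power for a single coefficient is not the measure of such a model. That is a good reason to keep the logistic model. It is no reason to make it the main test of which predictors matter. Calibration and prediction error were not examined here.
- **Outcome definition.** Response uses the last score obtained up to 12 months. A participant who misses the 1-month visit but is seen later still counts, so 258 need not be the response sample. A 1-month linear model changes the time point and the analysis set as well as the scale, and the plan would have to say so.
- **Importance.** These analyses are exploratory, carry nominal p-values and played no part in the sample-size calculation.

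**Conclusion.** The point holds as a limited one about an exploratory analysis. The prognostic model that the article names discards at least about a third of the information in the score, 36% at 50% response and more as the rate moves away from that.

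The loss of power is roughly 17 to 30 points for N = 258, r = 0.15 to 0.20 and response rates of 20 to 70%. It is about 17 to 20 points when response is between 40 and 60%, and nears 30 only when response is about 20%. It is 11 to 16 points at r = 0.10 and 2 to 7 at r = 0.30.

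A reader might want one figure for the loss. The documents do not support one, because predictor strength, response rate, standard deviation and correlation are all assumed. Nor does the point reach the primary comparison, which uses the full scale.

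**What to change.** In {20b}, make the main test of predictors a linear regression of the 1-month CAPS-5 total score on the candidate baseline predictors, adjusted for baseline CAPS-5 and treatment arm. Keep the logistic model of 10-point response, with its calibration checks, as a supplementary analysis that gives the probability of response. State that the linear model refers to 1 month, while response under {12} refers to the last score obtained up to 12 months.

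The cost is a sentence or two in the plan, with no new data, visits or staff; {20a} already contains a baseline-adjusted linear regression of 1-month change. There are two downsides. The main effects are expressed in CAPS-5 points rather than odds. Participants without a 1-month score do not contribute unless the predictors are entered in the mixed model instead.

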### Sample size {14}

A priori power analysis determined the sample size for comparing HOPE with an active control at the primary endpoint (1 month). Based on prior internet-delivered CBT work showing a between-group effect of Cohen’s *d* = 0.38 [8], we powered the trial to detect a conservative effect of *d* = 0.35 with 80% power at a two-sided *α* = 0.05 under 1:1 randomization. This yields *n* = 129 per group at the primary endpoint. To accommodate 10% data attrition (missing primary outcome), consistent with retention in other therapist-guided digital trials [11], we inflated the sample to *N* = 286 (143 per arm), expected to retain 129 per arm for analysis.

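### Calibration of the exploratory CAPS-5 response models rests on Hosmer–Lemeshow and calibration plots with no held-out or resampled data named; if both are run on the fitting data, neither responds to overfitting

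*Protocol article*

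**What the plan says.** Section {20b} of the protocol article plans prognostic models of CAPS-5 response and says that "logistic regression will be used with model calibration assessed by Hosmer–Lemeshow and calibration plots". It does not say on which data calibration is checked, how many predictors the models will hold, or what result would count as adequate calibration.

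The same sentence lists covariates: "PTSD/CPTSD severity, trauma type and timing, childhood adversity, comorbidity, perceived threat, education, employment, credibility/alliance". That list is given as examples for the moderation analysis (treatment-by-covariate interactions). The prognostic models have no list of their own.

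Response is defined in Outcomes {12} as a "minimum of 10 points improvement on the CAPS-5 between baseline and the participant’s last available measurement" up to the 12-month follow-up. Investigating predictors of treatment outcome is among the aims in Objectives {7}. Section {20a} sets a 5% level for every test, and the section on secondary outcomes treats secondary analyses as exploratory with nominal p-values. The article points to a full analysis plan on OSF, which is not shown here.

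**The concern.** A prognostic model fitted to a few hundred people tends to give predictions that are too extreme for new patients. A calibration assessment is where a reader would expect to see this. Hosmer–Lemeshow compares observed with predicted events in risk groups, and non-significance is usually read as good calibration. On the fitting data, maximum likelihood has already matched predictions to outcomes, so the comparison is nearly uninformative about overfitting. A plot drawn from the same data has the same limit.

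The trial could then report a non-significant test and a plot close to the diagonal for a model whose predicted probabilities do not transfer. What is at stake is how the predictor results are read, not the comparison of HOPE with control.

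**Working it through.** **Inputs from the article.** The sample-size section plans for d = 0.35 "with 80% power at a two-sided" 5% level, 129 per arm with the primary outcome and 286 randomised. Two arms of 129 give 258 for modelling. The level for Hosmer–Lemeshow is 0.05.

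**Inputs assumed.** The article gives no response rate, number of predictors or predictor strength.

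**The plan's own figure.** The article gives none for the prognostic models, so the only figure to reproduce is the sample size. 2 × (1.960 + 0.842)² / 0.35² = 2 × 7.85 / 0.1225 = 128.2, rounded up to 129 per arm. 129 / 0.90 = 143.3, against 143 stated. That is rounding and no part of this point.

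**Why the fitting data cannot show overfitting.** Maximum likelihood sets Σ(yᵢ − pᵢ) = 0 and Σxᵢⱼ(yᵢ − pᵢ) = 0 for each predictor j. Weighting the second set by the fitted coefficients gives Σlpᵢ(yᵢ − pᵢ) = 0, where lp is the linear predictor. These are the equations for the recalibration model logit P = a + s·lp at a = 0, s = 1. The in-sample intercept is therefore 0 and the slope exactly 1, whatever the number of noise predictors.

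**Test used.** C = Σ (O_g − E_g)² / [E_g(1 − E_g/n_g)] over 10 risk groups, with 8 df on the fitting data and 10 df on new data.

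**Simulation A.** N = 258, 50% response, three true predictors (log-odds 0.35 per SD), the rest noise; 1,000 trials each for 12, 16 and 20 coefficients, with the slope measured in 5,000 new patients. The 5-coefficient row comes from a repeat run on the same assumptions.

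| Coefficients | Non-significant, fitting data | Median slope, new patients (10th–90th percentile) |
|---|---|---|
| 5 | within 94–97% | 0.82 |
| 12 | 96% | 0.60 (0.46–0.79) |
| 16 | 96% | 0.51 (0.39–0.67) |
| 20 | 95% | 0.44 (0.34–0.58) |

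The repeat run gave 0.45 with 20 coefficients and pass rates of 94–97% from 5 to 20. For models with 12 to 20 coefficients and a slope below 0.8, 95–96% were still non-significant. With no true predictors the slope was about 0 and 95–96% were non-significant.

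**Simulation B, other assumptions.** N = 258, 40% response, five true predictors (log-odds 0.3 per SD), 1,500 runs per setting.

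| Coefficients | Non-significant, fitting data | Non-significant, new data | Slope, new data | c-statistic, fitting → new |
|---|---|---|---|---|
| 5 | 95% | 80% | 0.83 | 0.69 → 0.66 |
| 10 | 95% | 62% | 0.68 | 0.71 → 0.65 |
| 15 | 95% | 46% | 0.57 | 0.72 → 0.64 |
| 20 | 95% | 26% | 0.48 | 0.73 → 0.63 |
| 30 | 95% | 6% | 0.35 | 0.76 → 0.61 |

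**Sensitivity.** At N = 129, 258 and 286, pure-noise models included, the in-sample rate stayed at 94–96%. With 25% and 55% response it was 95–96%. After univariable screening from 25 candidates it was 97%, with an in-sample slope of 1.00 against 0.57 on new data. It fell clearly only in extreme models (91% and 81% with 70 and 90 coefficients at N = 258) or with a strong omitted quadratic term (87–92%).

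**What a slope means.** Take a patient with predicted log-odds 1.5, a probability of 82%, and assume no shift in the overall rate. A slope of 0.82 implies 1.5 × 0.82 = 1.23, or 77%. A slope of 0.60 implies 0.90, or 71%. A slope of 0.45 implies 0.675, or 66%.

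**The case against.** The strongest reply is that this reads too much into a condensed article. {20b} does not say that calibration is checked on the fitting data. The OSF analysis plan may contain internal validation, and an article commonly leaves that detail to the plan. This stands in part: in-sample use is an inference, and the absence of a validation statement is not by itself a fault. What remains is that the article does name its calibration tools, and on the fitting data those tools cannot do the job.

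Four further points are fair:

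- Hosmer–Lemeshow does respond to overfitting on data not used for fitting, as the new-data column shows. The weakness lies in the data set it is applied to.
- A reader might take the long covariate list as the prognostic predictor set. It belongs to the moderation analysis, so 12 to 20 coefficients is an assumption.
- A reader might infer that the test passes any model, however overfitted. The extreme settings show that it does not.
- The article sets no pass/fail rule and proposes no clinical use of predicted probabilities. The analysis is exploratory.

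The modelling sample may also differ from 258, because response uses the last available measurement up to 12 months. The result at N = 286 is the same.

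**Conclusion.** The point holds in conditional form and is minor. If Hosmer–Lemeshow and the plots are computed on the fitting data, they carry almost no information about overfitting at any plausible model size here. About 95% of models give a non-significant test, while the median slope in new patients runs from about 0.82 with 5 coefficients to about 0.45 with 20. The 95% barely depends on the assumptions. The slopes depend on the assumed number and strength of predictors, and a small model would suffer much less.

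The documents do not support the stronger statement that the trial will report badly calibrated models as sound. The data used for the check are not stated, the OSF plan is unseen, and no decision is tied to the test. The primary analysis and the treatment comparisons on secondary outcomes are untouched.

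**What to change.** In {20b}, do not rely on in-sample Hosmer–Lemeshow. Make the calibration assessment a bootstrap internal validation that repeats every modelling step, including any predictor selection, in each resample. Report the optimism-corrected calibration slope, calibration-in-the-large and c-statistic, and draw the calibration plot from the corrected predictions. Shrink the coefficients by the corrected slope, or use a penalised logistic fit. State the number of candidate coefficients in advance so that readers can judge the risk. If the OSF analysis plan already does this, a sentence saying so is enough.

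The cost is a short amendment, disclosed on OSF as the article promises for protocol changes, and some computing. No new data are needed. The reported performance will look less favourable.

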### Methods in analysis to handle protocol nonadherence and any statistical methods to handle missing data {20c}

All available data will be used in the models. All protocol deviations will be reported.

### Plans to give access to the full protocol, participant-level data, and statistical code {31c}

Consent to share deidentified information for future research is specified within the participant consent forms. Deidentified datasets will be available from the principal investigator upon reasonable request and with formal data transfer agreements for further research. The study protocol and the statistical code used will also be made available.

